## Abstract

**Background:**

With increasing age and longevity, the rising number of frail elders with complex and numerous health-related needs demands a coordinated health care delivery system integrating cure, care and welfare. Studies on the effectiveness of such comprehensive chronic care models targeting frail elders show inconclusive results. The CareWell-primary care program is a complex intervention targeting community-dwelling frail elderly people, that aims to prevent functional decline, improve quality of life, and reduce or postpone hospital and nursing home admissions of community dwelling frail elderly.

**Methods/design:**

The CareWell-primary care study includes a (cost-) effectiveness study and a comprehensive process evaluation. In a one-year pragmatic, cluster controlled trial, six general practices are non-randomly recruited to adopt the CareWell-primary care program and six control practices will deliver ‘care as usual’. Each practice includes a random sample of fifty frail elders aged 70 years or above in the cost-effectiveness study. A sample of patients and informal caregivers and all health care professionals participating in the CareWell-primary care program are included in the process evaluation. In the cost-effectiveness study, the primary outcome is the level of functional abilities as measured with the Katz-15 index. Hierarchical mixed-effects regression models / multilevel modeling approach will be used, since the study participants are nested within the general practices. Furthermore, incremental cost-effectiveness ratios will be calculated as costs per QALY gained and as costs weighed against functional abilities. In the process evaluation, mixed methods will be used to provide insight in the implementation degree of the program, patients’ and professionals’ approval of the program, and the barriers and facilitators to implementation.

**Discussion:**

The CareWell-primary care study will provide new insights into the (cost-) effectiveness, feasibility, and barriers and facilitators for implementation of this complex intervention in primary care.

**Trial registration:**

The CareWell-primary care study is registered in the ClinicalTrials.gov Protocol Registration System: NCT01499797

## Background

Worldwide, an increase in life-expectancy and ageing of the baby boom generation is leading to a vastly expanding population of elders. In the Netherlands, the number of people aged 65 years or above will increase from 2.4 million in 2010 to 4.6 million in 2040. Furthermore, life expectancy in the Netherlands will increase from 78.8 years to 84.5 years for males and 82.7 years to 87.4 years for females in the time span
[1].

Advancing age often implies an increase in the incidence of chronic diseases and multi morbidity with subsequent functional decline and social impairments, e.g. the loss of social support, financial limitations, and the lack of appropriate housing
[2,3]. The current system of health care delivery for community-dwelling frail elder people, with these numerous and complex health-related needs, is insufficient due to fragmentation and a lack of coordination and information exchange between health care professionals. Furthermore, sophisticated health information technologies that facilitate the essential processes of chronic care are not widely in use
[4,5]. Moreover, less urgent needs to optimally manage chronic illness and care for health related social and welfare problems are overshadowed by acute symptoms and concerns
[6,7]. Last, payment for and provision of medical and nursing care and social services are separated rather than integrated, and payment policies do not support supplemental services needed in providing chronic care
[4,5].

Frail elderly people are believed to benefit greatly from a coordinated chronic health care delivery system that integrates health and social care
[8]. A variety of models have been developed and tested over the last twenty-five years
[9,10]. This gave rise to an emerging vision of an optimal chronic care model in which health care organizations give priority to chronic care, health care providers are linked to community resources, chronic care management is separated from the acute care, elders receive self-management support, and evidence-based guidelines and clinical information systems are available to facilitate chronic care management
[6,7].

Few studies on such comprehensive chronic care models targeting frail elder persons have been conducted. Positive effects on functional performance
[11], on self-reported quality of health care
[12], and on informal caregiver satisfaction
[13] are suggested, although overall (review) findings are inconsistent
[14,15]. Furthermore, previous studies have shown some cost-saving implications through a postponement or reduction in residential or nursing home admissions, hospital admissions and emergency department visits
[11,13,16-18].

The CareWell-primary care program is a complex intervention integrating cure, care and welfare, that aims to prevent functional decline, improve quality of life and reduce or postpone hospital admissions and nursing home admissions in community-dwelling frail elderly. The program is based on existing chronic care models and is adapted to the Dutch health care system. It is designed as part of the National Care for the Elderly Program, which is launched in 2008 by the Netherlands Organization for Health Research and Development (ZonMW), in cooperation with the Nijmegen Network for the Care and Welfare of Elderly People
[4]. In developing the program, both health care professionals and a panel representing frail elderly and their informal caregivers were closely involved.

Complex interventions comprise multiple components that are interrelated or interdependent and therefore can be difficult to develop, document, evaluate and reproduce
[19]. To create a better understanding of how and why a complex intervention works, and to gain insight into costs and benefits, the framework for development and evaluation of complex interventions as published by the UK Medical Research Council is widely used
[20]. This framework emphasizes the value of including a process evaluation and an economic evaluation alongside the outcome evaluation. It provided the theoretical background for the design of our study. By gaining process information, we aim to detect gaps in implementation that might be responsible for the effectiveness of the program. Furthermore, we will explore why some general practices are more successful than others in improving the quality of care for their frail elderly patients
[21].

This paper presents the elements of the CareWell-primary care program as well as the design of both the CareWell-primary care (cost-) effectiveness study and process evaluation.

## Methods/design

### Study design and setting

The CareWell-primary care study has a pragmatic, cluster controlled design
[22]. It will be conducted in 12 general practices in (the municipality of) Nijmegen, the Eastern region of the Netherlands.

### Study population

#### Recruitment of general practices

General practitioners (GPs) are recruited to participate in the CareWell-primary care program through an invitational letter and a subsequent telephone call from one of the principal investigators. They are fully informed on the EasyCare Two-step Older persons Screening instrument (EasyCare-TOS)
[23], used to identify the frail elderly study participants, and on the elements of the program. GPs with a minimum of 300 patients aged 70 years or above in their practice population, a solid motivation to implement the program, and the organizational facilities required for implementation are eligible to participate in the intervention arm. After their informed consent, six GPs will be non-randomly assigned to the intervention arm.

A second group of GPs is similarly recruited to participate in the control group. These GPs receive information on the EasyCare-TOS, but no information on the CareWell-primary care program in order to prevent contamination bias. Furthermore, they are explicitly instructed to deliver ‘care as usual’, and not to start new collaborations with community nurses, elderly care physicians or gerontological social workers. No restrictions on existing collaborations are imposed. However, no multidisciplinary team collaborations comparable to those in the CareWell-primary care program are regularly available in usual care. Six GPs consenting to participation are non-randomly assigned to the control arm.

#### Study participants in the cost-effectiveness study

In each general practice, a random sample of fifty frail elders aged 70 years or above will be included in alphabetical order with the use of the EasyCare-TOS screening instrument
[23]. In step 1 of the EasyCare-TOS, the GP rapidly subdivides ‘not-frail’ from ‘(possibly-) frail’ elders by using prior, tacit knowledge. (Possible) Frail elders proceed to step 2, in which a trained community nurse or research assistant conducts a comprehensive geriatric assessment during a home-visit. The EasyCare-TOS step 2 questionnaire is shown in Additional file
1. In both study arms 300 frail elders will be included. Excluded from participation are (1) elders living in a residential or nursing home, (2) critically or terminally ill elders, (3) elders who are already enrolled in a case-management program, comparable to the CareWell-primary care program.

#### Informed consent

Eligible elders are asked for their willingness to participate in step 2 of the EasyCare-TOS and, in the intervention arm, in the CareWell-primary care program. Interested elders subsequently receive a written letter containing information on the EasyCare-TOS and, in the intervention group, the CareWell-primary care program. Finally, written informed consent is collected during the home-visits.

#### Study participants in the process evaluation

Next to a sample of patients and informal caregivers, all health care professionals participating in the CareWell-primary care program are included in the process evaluation; the GP’s, community nurses, gerontological social workers and elderly care physicians.

### Ethical considerations

The study has been reviewed by the local accredited medical review ethics committee: CMO region Arnhem-Nijmegen, registration number 2010/403. They concluded that formal ethical approval is not required, since the study does not involve research as covered by the Medical Research Involving Human Subjects Act. The study is registered in the ClinicalTrials.gov Protocol Registration System: NCT01499797.

### The intervention: the CareWell-primary care program

During a twelve-month intervention-period, the frail elders in the intervention group receive care according to the CareWell-primary care program. Figure 
1 shows a schematic representation of the EasyCare-TOS and the elements of the CareWell-primary care program.

**Figure 1 F1:**
[figure not shown]
Schematic representation of the EasyCare-TOS and the elements of the CareWell-primary care program.

The program consists of four key elements: (1) multidisciplinary team work, (2) proactive care planning, (3) case management, and (4) medication reviews. Each general practice will assemble one or two multidisciplinary teams, consisting of the GP, the community nurse, an elderly care physician and a gerontological social worker. These team members closely collaborate to ensure integration of cure, care and welfare. Face-to-face multidisciplinary team meetings will be held at least twice a year for each frail elder, in which care plans will be reviewed and adapted. In addition, the team members will be able to virtually communicate at all times within a secured web based health and welfare information portal (ZWIP)
[24]. This portal combines a shared Electronic Health Record with a communication tool for primary care professionals, which is accessible to all involved caregivers through a secured login procedure.

A proactive integrated care plan is formulated for each participant on enrollment in the program. These care plans will be based on the individual patients’ health-related goals and needs on the domains of cure, care and welfare as obtained with the EasyCare-TOS. The care plans will be stored in the ZWIP.

All elders will be assigned a case manager. This will be either the community nurse or the gerontological social worker, depending on the nature of the participants’ health-related needs. The case manager will be responsible for the organization of the multidisciplinary team meetings and for the coordination and monitoring of the proactive care process according to the care plan, as directed by the primary care physician. Moreover, the case manager will provide participant-support in goal setting and self-management by means of home-visits and telephone contacts.

The GP, community nurse and pharmacist will conduct a yearly medication review for those elders using five or more drugs for chronic use. Agreements on discontinuing inappropriate or unnecessary medications and starting medications in case of under-treatment will be incorporated in the care plan, thus ensuring appropriate drug treatment
[25].

In addition to these four key elements, four supporting elements facilitate the care delivery according to the program. First, we developed multidisciplinary practice guidelines on the medical treatment and nursing and social care of eight common geriatric syndromes: depression, dementia, chronic pain, falls, urinary incontinence, malnutrition, and vision and hearing impairment. These guidelines are presented as a job aid in the ZWIP. Second, a practice guideline concerning advance care planning is developed and presented in the ZWIP to promote a proactive dialog between frail elders and their GPs on wishes and expectations regarding medical treatment and end-of-life decisions. Third, procedure agreements regarding easy-access consultation of a geriatrician or a geriatric psychiatrist are constructed. Last, procedure agreements on hospitalization and discharge are made to facilitate the integration of primary- and in-hospital care, thus improving the interdisciplinary continuum of care.

### Tailored implementation strategies

At baseline, health care professionals in the intervention group are asked for their perceived barriers in the current practice of elderly care as well as for their expectations of the CareWell-primary care program by means of a structured questionnaire. This questionnaire is based on the baseline questionnaire developed in the Dutch Easy Care study
[26] and is pilot tested with peer group professionals. The information thus collected will be used to tailor the implementation strategies and activities, in order to facilitate optimal implementation of the CareWell-primary care program. A combination of implementation strategies and activities targeting both health care professionals and organizations will be used, addressing a variety of barriers for change
[27]: (1) different types of education (tailor-made meetings, coaching on the job, a helpdesk, and expert meetings) to overcome gaps in knowledge, attitude and skills needed to conduct the program, (2) persuasive communication and social influencing by means of large group meetings, in order to enhance both motivation and endurance for participation, (3) provision of additional information through a website, newsletters and written instructions, (4) providing feedback and advice to the participating professionals, and (5) financial reimbursement for all health care professionals and organizations to cover the extra efforts required by the program, to facilitate participation in the intervention. These implementation activities will start nine months before the actual start of the program and will be continued throughout the program.

### Cost-effectiveness study

#### Outcome measures and data collection

The primary outcome is the change in the level of functional performance in ADL between baseline and follow-up at twelve months, as measured with the Katz-15 index
[28].

Secondary outcomes are:

1. Quality of life, as measured with RAND-36
[29] and EQ-5D
[30]

2. Psychological and social functioning, as measured with a subscale of the RAND-36
[29]

3. Number of residential home, nursing home and hospital admissions

4. Mortality

Participants’ data are collected at baseline and at follow-up at twelve months with the EasyCare-TOS, in which baseline characteristics, the Katz-15 index, RAND-36, EQ-5D, and data on health service utilization and mortality are embedded.

Caregiver burden is measured with the Carer-Qol
[31], which is embedded in a structured caregiver questionnaire, to be filled in by the main informal caregiver.

Last, regular health care costs and costs of the CareWell-primary care program are collected with the EasyCare-TOS and through external sources, as shown in Table 
1.

**Table 1 T1:** Overview of sources used to obtain regular health care costs and costs of the CareWell-primary care program

**Costs**	**EasyCareTOS**	**External source**

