**Regular health care**		
regular GP contacts	X	electronic health record
out-of-office hours GP contacts	X	-
home care	X	home care organization
domestic care	X	municipality
medication	X	electronic health record
residential home admissions	X	-
nursing home admissions	X	-
day care in residential home	X	-
day care in nursing home	X	-
hospital admissions	X	-
physiotherapist	X	-
assistive devices	X	-

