#### Sample size calculation

The change in functional status between baseline and follow-up will be measured as a change in the sum-score on the Katz-15 index between baseline and 12 months
[28]. Although the Katz-15 index scores may be skewed, we expect these sum-score differences to have a normal distribution. For financial and logistic reasons, including 6 clusters in each study-arm is thought to be feasible. Each general practice is instructed to include 50 frail elderly. Based on the assumptions that 15% of eligible elders will decline informed consent and 20% will be lost to follow-up within the intervention-period of twelve months, the expected cluster size is 35. Using a two-sided alpha of 0,05, a power of 80%, an assumed between-clusters ICC of 0,01
[32], and a minimum cluster size of 35 with 2×6 clusters, we will be able to detect an effect size of >0,32, which is sufficient to detect even small differences
[33,34].

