#### Statistical analysis

The primary analysis will be performed adhering to the intention-to-treat principle. Descriptive statistics will be used to summarize characteristics of both participants and practices. Since the study has a hierarchical structure in which participants are nested within general practices, we will use hierarchical mixed-effects regression models / multilevel modeling approach to evaluate differences between the intervention and the control group in change in functional abilities between baseline and follow-up as measured with the Katz-15 index and all secondary outcomes. We will correct for the relevant covariates. Furthermore, the effect of the intervention on mortality, and on the time to hospital and nursing home admissions will be analyzed using survival analysis (Kaplan-Meijer curves) and Cox proportional hazard regression models. An additional sensitivity analysis will be conducted on a per-protocol analysis set, and on a subset of general practices in which the intervention is optimally implemented. Interim analyses will not be conducted. Statistical analyses will be performed using SPSS version 20.

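### Hospital, nursing home and residential home admissions have no dated source other than the baseline and twelve-month EasyCare-TOS, although time-to-admission models are planned and 20% loss is expected

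*Protocol article*

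**What the plan says.** All places are in the protocol article; no separate analysis plan is at hand.

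- **Outcome measures and data collection.** The number of residential home, nursing home and hospital admissions is the third secondary outcome and mortality is the fourth. Participants' "data are collected at baseline and at follow-up at twelve months with the EasyCare-TOS, in which baseline characteristics" and the outcome scales are contained; the same sentence adds that "data on health service utilization and mortality are embedded". No contact between the two time points is described.
- **Table 1 (cost sources).** The rows "hospital admissions X", "nursing home admissions X" and "residential home admissions X" mark the EasyCare-TOS and carry a dash under external source. In the same table, regular GP contacts and medication also have the electronic health record, home care has the home care organization, and domestic care has the municipality. Mortality has no row.
- **Sample size calculation.** The assumption is that "20% will be lost to follow-up within the intervention-period of twelve months". Death and other loss are not separated.
- **Statistical analysis (cost-effectiveness study).** Kaplan-Meier curves and Cox regression are planned for mortality and for time to hospital and nursing home admission. Residential home admission is not named for this analysis.
- **Economic evaluation.** Regular health care costs come from the sources in Table 1, and QALYs come from EQ-5D scores with the trapezium rule.

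**The concern.** A time-to-event analysis needs a date for each event and a known event-free period for everyone else. The only stated post-baseline source for admissions is one assessment at month twelve. This creates two gaps.

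1. For participants who are assessed at twelve months, admission dates must be reconstructed retrospectively at a single point.
2. For participants who die or leave before that point, no route is stated by which their admissions would be captured. In a frail population, these people may well have more admissions than those who complete.

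Reducing or postponing hospital and nursing home admissions is one of the program's stated aims (Abstract and Background). The same admissions also enter the cost side of both cost-effectiveness ratios, and a QALY for someone who dies needs a date of death. Loss of this information would leave admission counts, time-to-admission estimates and costs describing mainly those who completed.

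**Working it through.** **The plan's own figures.** No figure is given for admissions or mortality. The one design figure, a detectable effect size of 0.32 on Katz-15 change, reproduces: the design effect is 1 + (35 − 1) × 0.01 = 1.34, the effective size is 6 × 35 / 1.34 = 156.7 per arm, and (1.960 + 0.842) × √(2/156.7) = 0.316. It does not bear on this point. The figure that does is the 20% loss.

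**Step 1: what each participant group leaves behind, as written.**

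| Item | Assessed at 12 months | Died or lost before 12 months |
|---|---|---|
| GP contacts, medication | EasyCare-TOS and electronic health record | Electronic health record |
| Hospital, nursing home, residential home admissions | EasyCare-TOS only | No stated route |
| Date of death | Not applicable | Source not stated |

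A participant with no post-baseline information on admissions has no known event-free time and adds nothing to a Cox model. If a date of death is known but earlier admissions are not, treating that person as admission-free until death would undercount events.

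**Step 2: how many people.**

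- On 300 included per arm: 0.20 × 300 = 60 per arm, 120 in total.
- If the 15% non-consent comes off first: 0.85 × 300 = 255, and 0.20 × 255 = 51 per arm, 102 in total.

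**Step 3: share of admissions missed, if no other source is used.** Let k be admissions per person among those lost, relative to completers. Then share missed = 0.2k / (0.2k + 0.8). The 20% is from the plan; k is assumed.

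| k | Calculation | Share missed |
|---|---|---|
| 1.0 | 0.20 / 1.00 | 20% |
| 1.5 | 0.30 / 1.10 | 27% |
| 2.0 | 0.40 / 1.20 | 33% |

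**Step 4: why these are upper bounds for a given k.** If k is a ratio of rates, step 3 gives everyone lost a full year at risk, whereas a person who dies contributes less. With an average fraction f of the year at risk, the share is 0.2kf / (0.2kf + 0.8). At f = 0.5 (assumed, for illustration), k = 1 gives 0.10/0.90 = 11%, k = 1.5 gives 0.15/0.95 = 16%, and k = 2 gives 0.20/1.00 = 20%. For someone who drops out alive, f = 1 is appropriate, since their later admissions within the year are missed too.

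**The case against.** The best defence is that a journal article is condensed, and that completion of the EasyCare-TOS for someone who died or left is operational detail for the full protocol. Completion by the GP or a proxy is neither described nor excluded, and step 1 of the instrument is completed by the GP. This stands as far as it goes: that dates rest on a participant's own memory is an inference, and the percentages hold only if no other source is used. It does not remove the point. Table 1 has a column for external sources, fills it for four items and enters a dash for these three. That is a stated choice, and no later analysis plan can recover dates that were not collected.

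A reader might infer four stronger things that the article does not support.

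- **That deaths go unrecorded.** Mortality is listed as an item within the EasyCare-TOS, so someone must enter it. Table 1 concerns costs, so its dashes say nothing about deaths. What is missing is the source of the date.
- **That the primary analysis is really one of survivors with an assessment, despite the statement that "The primary analysis will be performed adhering to the intention-to-treat principle".** Handling of death and missing Katz-15 data may sit in the analysis plan, which is not at hand.
- **That loss will differ between arms.** One loss rate is assumed, and one instrument and schedule apply to everyone. Case management might aid retention, but nothing in the article shows it.
- **That the Cox models cover residential home admission.** They are planned only for mortality, hospital and nursing home admission.

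It is also fair to say that the article does not show that the GP record holds dated admissions. The fix therefore includes a check.

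**Conclusion.** The point holds in limited form. For all three admission types the EasyCare-TOS at baseline and twelve months is the only stated source. Time-to-admission models and costs are to be built on it, and the plan expects one participant in five to be lost. No route is stated for admissions before death or dropout, nor a source for dates of death.

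If nothing else is used, about 20% of admissions would be missed with equal risk in those lost and completers, and 27% to 33% with 1.5 to 2 times the risk. These shares rest on the plan's 20% loss, an assumed risk ratio, no capture at all among those lost, and a full year at risk for each of them. The last assumption makes them upper bounds.

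The effect falls on secondary outcomes and on the cost and QALY calculations. It does not reach the Katz-15 primary endpoint, so it is worth correcting but is not a condition for the primary analysis.

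**What to change.** 1. In Table 1 and in Outcome measures and data collection, add the GP electronic health record, already used for GP contacts and medication, as the dated source for deaths and for hospital, nursing home and residential home admissions. Apply it identically in both arms and to all consented participants, including those without a twelve-month assessment. Keep the EasyCare-TOS as a complement.
2. Run the time-to-event and cost analyses on all included participants, with record follow-up until death, leaving the practice or twelve months, whichever comes first.
3. Where an institutional admission is the reason for leaving the practice, count it as the event rather than as censoring. Otherwise the censoring would itself be informative.

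**Cost.** A few more fields in a record source already in use, possibly an extension of the consent wording, and a check before data collection that the record holds these dates in both arms.
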